#### Study 1: Statistical Analysis and Anticipated Results

A sample size of 30 was selected as a starting number of patients for the clinical trial. A priori analysis indicated that for a sample size of 30, we would need a large effect size (*f* = 0.42) in order to reach statistical significance (*p* ≤ 0.05). In our previous study of six patients receiving vCR treatment for 3 months, using a paired samples *t*-test to compare MDS-UPDRS III scores pre- and post-treatment, the effect size was large (*d* = 1.011) (17). Based on this, our large *f* effect size of 0.42 may be reasonable. Nevertheless, an interim analysis will be performed by an un-blinded, experienced statistical research personnel, who is unaffiliated with the study team and does not report to any study team member, the principal investigator, nor any neurologist involved in the studies. This interim analysis will be performed when 16 patients have completed the 3-month mark, with eight belonging to the sham group and eight belonging to the vCR group. Results from the interim mixed factorial analysis of variance (ANOVA), will allow us to recalculate our desired sample size.

A 2 (sham vs. real vCR) by 4 (baseline, 3, 6, and 7 months) mixed factorial ANOVA will be done separately on the following measures: MDS-UPDRS I, II, III, IV, Levodopa equivalent daily dose (LEDD), EEG sensorimotor related evoked components, vCR resting EEG beta power response, vibratory temporal discrimination, speech assessments, UPSIT, PDSS, PDQ-39, FOG, and gait measurements obtained from the APDM Mobility Lab.

Statistically, for patients who received real vCR, we hope to see significant improvement in all measures by 6 months and expect to see no significant worsening when comparing assessments done after the pre-planned 1-month pause in stimulation at 7 months. In addition, we expect to see no significant improvements in the sham group patients.

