### Study 1 Design: Main Phase—Double Blind Sham-Controlled

We will perform a 7-month, double-blind, sham-controlled study including 30 PD patients randomly placed into either active vCR (*n* = 15) or a sham (*n* = 15) condition. All personnel and PD patients will be completely blinded to which stimulation pattern patients obtain. Parkinson's patients will receive vCR or sham stimulation for a total of 4 h a day (2 times 2 h a day with a break in between the 2-h sessions) at home for 6 months. To measure long-term effects, patients will pause stimulation for 1 month after the 6-month follow-up appointment.

#### Assessments: Study 1

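### The interim look re-sizes the trial from an un-blinded 8-versus-8 result at 3 months: the new N would be mostly noise, and the final 5% level is at risk under some re-sizing rules

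*Protocol article*

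**What the plan says.** All of this is in the protocol article, under Study 1: Statistical Analysis and Anticipated Results, unless another place is named.

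- **Starting size.** "A sample size of 30 was selected as a starting number of patients for the clinical trial". The Study 1 design section splits them equally: "randomly placed into either active vCR (*n* = 15) or a sham (*n* = 15) condition".
- **Planning effect.** With 30 patients a Cohen f of 0.42 is said to be needed "in order to reach statistical significance (*p* ≤ 0.05"). Support comes from six earlier patients compared before and after treatment, where "the effect size was large (*d* = 1.011"). The article concludes that "our large *f* effect size of 0.42 may be reasonable".
- **Interim.** The next sentence opens with a word of reservation and introduces the interim analysis, done by an un-blinded analyst outside the study team. "This interim analysis will be performed when 16 patients have completed the 3-month mark, with eight belonging to the sham group" and the other eight to the vCR group.
- **Use of the interim.** "Results from the interim mixed factorial analysis of variance (ANOVA), will allow us to recalculate our desired sample size".
- **Primary outcome.** The Abstract names off-medication MDS-UPDRS III after 6 months of treatment.

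The article states no re-sizing formula, no limits on N, and no adjustment of the final test.

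**The concern.** Three choices are fixed in the text: a comparison by arm, eight patients per arm, and the 3-month visit. Together they make a poor basis for a sample size.

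An effect estimated from eight per arm is very imprecise, and required N varies with the inverse square of that effect, which magnifies the error. The effect is also taken at 3 months, while the trial is judged at 6. Finally, once N depends on the observed treatment effect and the same patients enter the final analysis, an ordinary test at 0.05 need not keep its level.

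At stake are a trial re-sized far too small or far too large by chance, and a primary p-value whose error rate is open to challenge. The Abstract, Introduction and Conclusion all say the results are meant to support FDA clearance.

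**Working it through.** **Inputs from the article:** N = 30, 1:1; f = 0.42; p ≤ 0.05; interim on 8 versus 8 at 3 months; primary outcome at 6 months. **Assumed, because not given:** 80% power; two-sided testing; within-patient correlation 0.5 (step 1 only); limits on N; correlation ρ between 3- and 6-month outcomes, from 0 to 1; no dropout.

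**1. The plan's own figure.** For the between-group test of a repeated-measures ANOVA with m = 4 visits, λ = f²·N·m / (1 + (m − 1)·0.5) = 0.1764 × 30 × 4 / 2.5 = 8.47. With 1 and 28 degrees of freedom this gives 80.2% power, so f = 0.42 at N = 30 reproduces. For two equal groups d = 2f = 0.84. A comparison at a single visit with d = 0.84 has only 60% power at 15 per arm.

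**2. Precision at the interim.** SE(d) = √(2/8 + 0.84²/(2 × 16)) = √(0.250 + 0.022) = 0.52. An observed d of 0.84 has a 95% confidence interval of −0.20 to 1.85.

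**3. What that does to N.** n per arm = 2(1.96 + 0.842)²/d² = 15.7/d².
- d = 0.84: 15.7/0.706 = 22.3, so 23 per arm.
- One SE lower, d = 0.32: 15.7/0.102 = 153 per arm.
- One SE higher, d = 1.36: 15.7/1.85 = 8.5, so 9 per arm.

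Simulating the interim with true d = 0.84 gives a total N with median 43 and quartiles 21 to 120. About 5% of interims have the wrong sign. Among those with d > 0, n per arm has median 20 and quartiles 10 to 50.

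**4. Sensitivity to the sizing model.** Suppose the interim ANOVA were as efficient as the four-visit analysis that has 80% power at 30. The expected z at 16 patients is then 2.80 × √(16/30) = 2.05, with quartiles 2.05 ± 0.67 = 1.38 and 2.72. Required total N = 16 × (2.80/z)² runs from about 17 to about 66 between the quartiles. That is still a fourfold spread, under a favourable assumption.

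**5. Type I error.** The simulation has no true effect, N set for 80% power at the observed 3-month d, and an unadjusted two-sided 0.05 test of the 6-month outcome on all patients.

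| Rule for n per arm | Type I error |
|---|---|
| Set from observed d, 15 to 60 | 5.0% (ρ = 0), 5.4% (0.5), 5.7% (0.7), 6.4% (0.9), 6.8% (1.0) |
| May also shrink, cap 30 or 60 | 6.1% to 8.0% (ρ = 0.7 to 1.0) |
| May shrink to 8 or grow to 200 | 5.7% (ρ = 0.5), up to 8.5% (ρ = 1.0) |
| Raised only if the required n is at most 60, otherwise 15 | 4.7% to 4.9% |

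Repeat runs of the first row agree to within 0.2 percentage points. The worst case for any rule with 15 to 60 per arm at ρ = 1 is 7.0%.

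**6. The alternatives.** Re-estimation from the blinded pooled variance, with d held at 0.84 and limits of 15 to 60 per arm, gives 4.95% and 15 to 38 per arm (5th to 95th percentile). An inverse-normal combination with weights fixed at 8/15 and 7/15 gives 4.99%.

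**The case against.** **The rule may sit in a document not shown.** A journal article commonly leaves the formula, the limits on N and any adjustment to the full protocol or SAP. The 0.05 criterion appears only in the effect-size sentence, not as the final decision rule. This stands: one can say only that no error control is stated here. A reader might infer that the final test exceeds 5%. The article does not support that, because under one plausible rule there is no inflation.

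**The ANOVA also yields a variance.** It is nowhere said outright that the observed effect sets N. That is correct, but the interim is introduced in answer to doubt about the effect size, and a variance alone would need neither an un-blinded analyst nor a split by arm. The effect-based reading is the natural one.

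**Shrinkage is speculative.** Calling 30 a starting number suggests growth, so the 5% to 7% range is the more relevant one.

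**Two further inferences fail.** A reader might say that the planned 2 by 4 ANOVA cannot be run at 3 months. The interim is called only a mixed factorial ANOVA, and group by baseline and month 3 is one. A reader might also say that the new N reveals the interim effect to the blinded team. That needs a rule known to the team, and the analyst is described as independent of it.

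**The study is modest in aim.** The Summary and Outlook section calls Study 1 proof-of-concept, corresponding to phase IIA. This lowers the severity.

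None of this answers the imprecision of an 8-versus-8 effect or the mismatch of 3 and 6 months. An adjusted final test in a SAP would protect the level but would not make the new N informative.

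**Conclusion.** The concern holds in two parts of different strength.

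**Firm:** if the observed effect sets N, the new N is mostly noise. The middle half of results runs from 21 to 120 patients in total when the true d is 0.84, and even a favourable sizing model leaves a fourfold spread. The effect used is also not at the primary time point. This rests on assumed 80% power and on the natural reading of the text.

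**Conditional:** an unadjusted final test at 0.05 can exceed its level, depending on a rule the article does not state. The figure is about 5% to 7% if N grows for small observed effects, up to about 8% if it may also shrink (8.5% at the widest limits tried), and no inflation if it grows only for promising results. Inflation is a risk left open, not an established result.

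Severity is moderate: a cheap improvement, not an essential correction, for a study that describes itself as proof-of-concept.

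**What to change.** **Preferred.** Replace the interim ANOVA by blinded re-estimation. Pool off-medication MDS-UPDRS III from the first 16 patients without arm labels, estimate the SD, and recompute N for a between-group difference in points that is fixed before the interim. N never falls below 30, and a maximum is stated.

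**If the un-blinded effect must be used.** Before the interim, write down the re-sizing rule and the minimum and maximum N. Test the 6-month primary outcome with a combination test whose stage weights are fixed in advance (Cui-Hung-Wang or inverse-normal; for example 8/15 and 7/15). Assign patients to stages by whether they were among the 16 used at the interim.

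**Cost.** Protocol and SAP wording only. With the first option N can no longer be tuned to the observed effect, so doubt about the effect size must be settled by the choice of the difference in points, which the article does not give. With the second option the combination test loses a little efficiency, and the new N stays as imprecise as shown above.

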## Abstract

Enhanced neuronal synchronization of the subthalamic nucleus (STN) is commonly found in PD patients and corresponds to decreased motor ability. Coordinated reset (CR) was developed to decouple synchronized states causing long lasting desynchronization of neural networks. Vibrotactile CR stimulation (vCR) was developed as non-invasive therapeutic that delivers gentle vibrations to the fingertips. A previous study has shown that vCR can desynchronize abnormal brain rhythms within the sensorimotor cortex of PD patients, corresponding to sustained motor relief after 3 months of daily treatment. To further develop vCR, we created a protocol that has two phases. Study 1, a double blinded randomized sham-controlled study, is designed to address motor and non-motor symptoms, sensorimotor integration, and potential calibration methods. Study 2 examines dosing effects of vCR using a remote study design. In Study 1, we will perform a 7-month double-blind sham-controlled study including 30 PD patients randomly placed into an active vCR or inactive (sham) vCR condition. Patients will receive stimulation for 4 h a day in 2-h blocks for 6 months followed by a 1-month pause in stimulation to assess long lasting effects. Our primary outcome measure is the Movement Disorders Society-Unified Parkinson's Disease Rating Scale (MDS-UPDRS) part III off medication after 6 months of treatment. Secondary measures include a freezing of gait (FOG) questionnaire, objective motor evaluations, sensorimotor electroencephalography (EEG) results, a vibratory temporal discrimination task (VTDT), non-motor symptom evaluations/tests such as sleep, smell, speech, quality of life measurements and Levodopa Equivalent Daily Dose (LEDD). Patients will be evaluated at baseline, 3, 6, and 7 months. In the second, unblinded study phase (Study 2), all patients will be given the option to receive active vCR stimulation at a reduced dose for an additional 6 months remotely. The remote MDS-UPDRS part III off medication will be our primary outcome measure. Secondary measures include sleep, quality of life, objective motor evaluations, FOG and LEDD. Patients will be evaluated in the same time periods as the first study. Results from this study will provide clinical efficacy of vCR and help validate our investigational vibrotactile device for the purpose of obtaining FDA clearance.

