The following outcome measures and their descriptions will be administered to patients. The *MDS-UPDRS parts IA, IB, II, III*, and *IV* (29). The MDS-UPDRS parts IA and IB concerns non-motor experiences of daily living, in which IA is assessed by the study's main MDS-UPDRS movement disorders evaluator and IB is self-reported. Part II is motor experiences of daily living and is self-reported. Part III is the in-person motor evaluation assessed by the study's main MDS-UPDRS movement disorders evaluator. In addition, part III will be video recorded and sent to the three blinded video MDS-UPDRS III raters. Patient recordings will be evaluated after each patient completes his or her 7-month visit. Video raters will additionally be blinded to the date of administration. Part IV incorporates patient details on motor complications with the study's main MDS-UPDRS movement disorders evaluators observations and judgements. The *PD Quality of Life Questionnaire-39* (*PDQ-39*) (32) is a self-report questionnaire that examines health related difficulties specific to PD in eight quality of life categories within the last month. The *Parkinson's disease sleep scale* (*PDSS-2*) (33) examines PD related sleep issues during the past week. The *University of Pennsylvania Smell Identification Test* (*UPSIT*) (34) is a smell test comprised of 40 odors, in which patients try to correctly identify the odorant presented. Patients will also take a tolerability and usability questionnaire regarding the vCR device. We will perform a *vibratory temporal discrimination task* (*VTDT*) that consists of two vibratory bursts, with one burst delivered to the index finger and one burst to the middle finger. Each burst will start randomly on either the index or middle finger. This procedure will be performed on the right and left hand separately. The patient is instructed to judge if he/she felt a delay between the two vibratory bursts. This task was designed as a possible calibration method for future vCR studies by serving as a sensitivity measure for vibratory temporal changes, in which reduced perceived vibratory time differences correspond to increased vibratory temporal discrimination. Patients will also undergo clinically established *speech and voice assessments*. Speech samples will be collected at a sampling rate of 44,100 Hz on a laptop using the Praat Speech Analysis program (Version 5.4, University of Amsterdam). To collect samples, a head-worn, unidirectional microphone will be placed over the participant's ears and the microphone will be adjusted so that it is 6 cm from the participant's mouth. Specific samples will include sustained vowel phonations, sentence and paragraph length reading passages, and spontaneous speech. From these samples, speech and voice assessments will be conducted including measures of articulatory precision, speech intelligibility, speech rate, auditory-perceptual ratings of voice, and acoustic measures of vocal fundamental frequency, vocal intensity, and fundamental frequency and intensity variability. Additionally, the sentence intelligibility portion of the Assessment of Intelligibility in Dysarthric Speech (AIDS) (35) and patient self-assessment scales of Communicative Participation Item Bank (CPIB) (36) and the voice handicap index (VHI) (37) will be collected. For objective measures, patients will perform the *Kinesia ONE* motor evaluation, which uses a wearable accelerometer to assess motor activities similar to the MDS-UPDRS III and record their Parkinson's medication intake. The *Ambulatory Parkinson's Disease Monitoring* (*APDM*)'s Mobility Lab system will be used to measure objective gait disturbances. Lastly, the patient will also complete three different types of tasks during which *EEG* will be recorded. The first is a *sensorimotor EEG task*, in which patients receive a single vibratory stimulus to a random finger (excluding the thumb) on their non-dominant hand and are instructed with their dominant hand to push the response pad as fast as possible when they feel the vibratory burst. Each finger receives an equal number of vibratory pulses (50 per finger, equaling 200 trials) in a randomized order. Cortically, we expect to look at motor evoked potentials in response to cued vibration and their amplitude and latency changes throughout the course of treatment. Reaction time will also be documented. Additionally, we will record *vibration-only evoked potentials* in which we look at how two different types of vibratory pulses (high- and low- amplitude) affect different motor and sensory areas of the brain. The last task will be a recording done while the patient is at rest (*spontaneous EEG*). Patients will receive either active vCR or sham depending on the condition to which they were randomly assigned. For this task, we want to replicate our previous finding of decreased high beta band power (21–30 Hz) (17) for patients who received real vCR and quantify differences in activated brain areas in response to sham or active vCR. The MDS-UPDRS III off medication will be used as our primary outcome measure. All other measures are considered secondary.

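### The primary outcome is off-medication MDS-UPDRS III at 6 months, but no term of the one stated final analysis, a 2 by 4 ANOVA, is the 6-month active-versus-sham difference

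*Protocol article*

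**What the plan says.** The Abstract gives the Study 1 primary outcome as the MDS-UPDRS "part III off medication after 6 months of treatment". The Study 1 assessments text repeats the scale without a time point: "The MDS-UPDRS III off medication will be used as our primary outcome measure. All other measures are considered secondary". Summary and Outlook gives the aim of Study 1 as showing efficacy against sham. Together these pose one question: active versus sham, off medication, at month 6.

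The section Study 1: Statistical Analysis and Anticipated Results names one final analysis: "A 2 (sham vs. real vCR) by 4 (baseline, 3, 6, and 7 months) mixed factorial ANOVA will be done separately". It applies alike to part III and to every listed secondary measure. The section does not say whether group, time or group-by-time decides the trial. Its anticipated results are worded within arms: improvement under vCR by 6 months, no worsening at 7 months, no improvement under sham.

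The month-7 visit is off stimulation: "patients will pause stimulation for 1 month after the 6-month follow-up appointment". On size, the article says "A sample size of 30 was selected as a starting number of patients for the clinical trial" and that with this number "we would need a large effect size", f = 0.42. An interim mixed ANOVA, run when 16 patients reach month 3, is to be used to recalculate the sample size.

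**The concern.** A 2 by 4 mixed ANOVA yields three tests, and none of them is the month-6 arm difference.

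- **Group** compares the arms on the average of all four visits. At baseline the expected difference is zero by randomisation, and at month 7 stimulation has been off for a month.
- **Time** does not compare the arms.
- **Group by time** (3 df) asks whether the arm difference varies over any of the four visits. A difference at month 3 alone or month 7 alone can make it significant.

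A real month-6 benefit could therefore be missed if the main effect decides. A positive result could be declared without a month-6 benefit if the interaction decides. Because no term is named, the choice between the two could also be made after the data are seen. The results are intended to support FDA clearance, so the deciding test needs to be fixed in advance.

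**Working it through.** **Inputs from the article.** 30 patients, 15 per arm; four visits; alpha 0.05; f = 0.42. For two equal groups d = 2f = 0.84.

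**Assumed, because the article does not give them.** 80% power behind f = 0.42; visit correlation rho, equal for all pairs of visits, from 0.3 to 0.8; the effect profiles below. The pilot d = 1.011 is a paired pre-post figure from six patients without a control arm, so it is not used as a between-arm effect.

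**Step 1: reproduce f = 0.42.** For the four-visit group main effect, lambda = f² × N × m / (1 + (m − 1) × rho), with df 1 and 28. At rho = 0.5, lambda = 0.1764 × 30 × 4 / 2.5 = 8.47, and power is 80.2%. Exactly 80% needs f = 0.419. At the same power and rho, the interaction needs 0.218 and a single-visit comparison 0.530. The match is not unique: 90% power with rho = 0.3 gives 0.423 for the same term. So the stated f is consistent with a calculation on the group main effect, but this is not proved.

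**Step 2: dilution of the main effect.** With no difference at baseline and d = 0.84 at months 3, 6 and 7, the average is 0.84 × 3/4 = 0.63, so f = 0.315. At rho = 0.5, lambda = 0.0992 × 30 × 4 / 2.5 = 4.76, and power falls from 80% to 56%.

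**Step 3: the interaction.** lambda = (sum of squared deviations of the visit differences from their mean) / ((1 − rho) × 2/15), with df 3 and 84. For the profile 0, 1, 1, 1 the sum is 0.84² × (0.75² + 3 × 0.25²) = 0.84² × 0.75. For 0, 1, 0, 0 (month 3 only) it is 0.84² × (0.75² + 3 × 0.25²), the same value. The test therefore cannot tell a sustained effect from one at month 3 only.

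**Step 4: month-6 comparison adjusted for baseline.** lambda = d² / ((1 − rho²) × 2/15), with df 1 and 27, gives 73% / 87% / 96% at rho 0.5 / 0.7 / 0.8. The formula ignores chance baseline imbalance. Simulation, 20,000 trials per setting, gives 71% / 86% / 95%, used below.

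Probability of a significant result at rho 0.5 / 0.7 / 0.8:

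| True difference at 0, 3, 6, 7 months (× 0.84) | Group main effect | Group by time | Month 6, baseline-adjusted |
|---|---|---|---|
| 0, 1, 1, 1 | 56 / 47 / 44% | 63 / 86 / 97% | 71 / 86 / 95% |
| 0, 0.5, 1, 0 | 18 / 16 / 15% | 59 / 83 / 95% | 71 / 86 / 95% |
| 0, 1, 0, 0 | 11 / 10 / 9% | 63 / 86 / 97% | 5 / 5 / 5% |
| 0, 0, 0, 1 | 11 / 10 / 9% | 63 / 86 / 97% | 5 / 5 / 5% |

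The first two columns are exact noncentral-F values; simulation gives main-effect power within about one point (57 / 48 / 44% in the first row). At rho = 0.3 the first row is 68% for the main effect, 47% for the interaction and 64% (formula) for month 6, so the main effect is not inferior at every correlation.

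**The case against.** The article condenses a fuller plan, and a separate SAP may name a month-6 contrast; one can be computed from the same ANOVA. Keeping baseline as a level of time is a legitimate way to test differential change. The interaction uses each patient's own baseline and, for a sustained effect, matches the adjusted month-6 comparison at correlations of 0.7 and 0.8. The scenario with d = 0.84 at month 3 and none at month 6 is stylised, since stimulation continues unchanged to month 6. The anticipated results also show that month 6 is not ignored.

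Much of this stands, and it limits the point. A reader might infer that the plan discards precision in general; that is true of the main effect at moderate to high correlation, not of the interaction. A reader might infer that any patient with a missed visit is dropped, or that the F-test will be left uncorrected for non-sphericity. The article specifies neither, so neither can be charged to the plan. Nor can it be said that the full plan lacks a month-6 contrast.

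What does not stand is that the matter is only missing detail. The article fixes an endpoint and fixes a test, and the two do not match. Its month-6 expectations are within-arm: improvement under vCR and none under sham do not amount to a test of vCR against sham. The month-3-only case is an illustration; a significant 3-df interaction does not locate the difference at month 6 under any profile.

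**Conclusion.** The point holds as a mismatch between the stated primary endpoint and the stated final analysis. If the group main effect decides, a sustained d = 0.84 is detected with about 56% / 47% / 44% power at visit correlations of 0.5 / 0.7 / 0.8, against 71% / 86% / 95% for the baseline-adjusted month-6 comparison. If the effect builds up and is lost after the pause, main-effect power is 18% or less. If the interaction decides, power is good, but the test is not specific to month 6: it is significant in 63% / 86% / 97% of trials with an effect at month 3 only.

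These figures rest on assumed correlations, assumed effect profiles and d = 2f; the mismatch itself does not. A reader might also conclude that the sample size rests on the diluted main effect. The f = 0.42 match makes that plausible, but other combinations of power and correlation come close, and the article states neither.

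**What to change.** Name one primary test: the active-minus-sham difference in off-medication MDS-UPDRS III at month 6, adjusted for the baseline score. Estimate it by ANCOVA, or as the month-6 contrast of a mixed model for repeated measures with months 3, 6 and 7 as outcomes, baseline as covariate, arm, visit and arm by visit, using all available data from randomised patients. Report months 3 and 7 as secondary contrasts. Add the 6-month time point to the primary-outcome sentence in the Study 1 assessments text. If a SAP already specifies a month-6 contrast, bring the article's wording into line with it.

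Restate the f = 0.42 sentence for this test, with its power and assumed baseline correlation, and align the interim sample-size recalculation. The interim is triggered at month 3, when month-6 scores need not be available for all 16 patients, so the text should say how the month-3 data inform the month-6 calculation.

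Cost: no new patients, visits or measurements. The omnibus ANOVA stops being the headline test, and the interim and sample-size wording must be reworked.

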Taken together, we believe that vCR has the potential to drastically improve motor abilities during and post treatment, decrease patient medication intake and potentially slow disease progression in a way that is non-invasive and presents little to no side effects. The current study protocol: *Vibrotactile coordinated reset: a non-invasive treatment for Parkinson's disease*, aims to understand the therapeutic benefits of vCR in a larger sample size, test against a dedicated sham pattern, study vCR effects on not only motor outcomes, but voice, speech, sleep and other non-motor symptoms, study vCRs long-lasting effects, and finally a vCR dosing regimen all within a 14-month clinical study protocol. Together, results from this study will demonstrate clinical efficacy of our vCR stimulation pattern and vibrotactile device for the purpose of acquiring Food and Drug administration (FDA) clearance.

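### Study 1 reads the lasting effect after the one-month pause from a non-significant change within the vCR arm; the month-7 difference from sham should be the stated estimate

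*Protocol article*

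**What the plan says.** The Introduction lists among the aims to "study vCRs long-lasting effects". The Study 1 design section gives the pause that purpose: "To measure long-term effects, patients will pause stimulation for 1 month after the 6-month follow-up appointment". Both arms pause, and the allocation is 15 to 15.

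The analysis is in the section Study 1: Statistical Analysis and Anticipated Results: "A 2 (sham vs. real vCR) by 4 (baseline, 3, 6, and 7 months) mixed factorial ANOVA will be done separately" on each listed outcome. The same section then says what the authors look for, arm by arm. In vCR patients they hope for significant improvement by 6 months, and they "expect to see no significant worsening when comparing assessments done after the pre-planned 1-month pause in stimulation at 7 months". In sham patients they expect no significant improvement. No vCR-versus-sham contrast at month 7 is named, and no margin says how much worsening would still count as a lasting effect. The Abstract places the primary outcome, off-medication MDS-UPDRS III, at 6 months.

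**The concern.** Failing to find a significant deterioration is not the same as showing that a benefit was kept. With 15 patients, the test can miss a sizeable loss. The reading also stays inside one arm, although the sham patients put their gloves away at the same time. They are the concurrent control for fading placebo response, natural change and rater drift.

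Two errors are possible. A lasting benefit could be inferred when about half of it has gone, or when the improvement was non-specific and present in both arms. Conversely, persistence could be denied when both arms drift down together and the difference between them is intact. The article offers its results in support of FDA clearance, so the reading of the pause should rest on the randomised comparison.

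**Working it through.** **Inputs from the article.** 15 patients per arm; significance level 0.05; detectable f = 0.42 for 30 patients; pilot effect d = 1.011 from a paired t-test in six patients over 3 months.

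**Assumptions.** Two-sided tests; 15 completers per arm; normal data; equal variances and equal correlation rho between visits; the pilot d standardised by the SD of the change (dz), with the month 6 to 7 change having that same SD.

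**The plan's own figure.** For the arm main effect over m = 4 visits, lambda = f² × N × m / (1 + (m − 1) × rho). With f = 0.42, N = 30 and rho = 0.5 this is 0.1764 × 120 / 2.5 = 8.47. On 1 and 28 df the power is 80.2%, so f = 0.42 is reproduced at an assumed 80% power. It concerns the arm effect averaged over visits. The article gives no figure for the pause.

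**Step 1: how often the within-arm check is passed.** The check is passed when the paired t statistic does not exceed t(14; 0.975) = 2.145 in the direction of worsening. The statistic is noncentral t with noncentrality dz × √15.

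| Share of pilot effect lost | dz of worsening | Noncentrality | Check passed |
|---|---|---|---|
| none | 0 | 0 | 97.5% |
| a quarter | 0.253 | 0.98 | 85% |
| half | 0.506 | 1.96 | 55% |
| all | 1.011 | 3.92 | 5% |

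Detecting a worsening with 80% power needs dz = 0.78, which is 0.78 / 1.011 = 77% of the pilot effect.

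The half-lost figure depends on the effect assumed. Taking f = 0.42 as d = 2 × 0.42 = 0.84 SD, the loss is 0.42 SD and dz = 0.42 / √(2(1 − rho)). The check is then passed 67%, 50% and 33% of the time at rho 0.5, 0.7 and 0.8. If f = 0.42 averages a zero baseline difference with three equal later ones, the effect is 0.84 × 4/3 = 1.12 SD, and the figures are 48%, 26% and 11%.

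**Step 2: adding improvement by month 6, with no change in either arm.** Significant improvement occurs 2.5% of the time by chance. In 200,000 simulated trials the check is then passed in about 83% of those cases, so the joint pattern occurs about 0.025 × 0.83 = 2% of the time.

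**Step 3: the same lasting improvement in both arms (vCR minus sham = 0).**

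- At dz = 1.011 in each arm, the vCR-arm pattern (improved by month 6, not significantly worse at month 7) appears about 93% of the time. Sham escapes significance about 5% of the time, so the three-part pattern appears in about 0.93 × 0.05, roughly 4 to 5% (about 4% by simulation).
- At dz of about 0.54, each arm has about a 50% chance of significant improvement. The vCR-arm pattern appears about 47% of the time, and the three-part pattern about 0.47 × 0.50 = 24%. This judges sham at month 6. If sham must also show no significant improvement at month 7, the same simulation gives about 16%.

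**Step 4: the direct contrast at month 7.** With no vCR effect, a significant favourable difference occurs 2.5% of the time, whatever improvement the arms share. In units of the outcome SD, the 95% CI half-width is t(27; 0.975) × √(2/15) × √(1 − rho²), where rho is the correlation with baseline. That is 2.052 × 0.365 = 0.75 SD unadjusted, and 0.75 × √(1 − 0.49) = 0.54 SD at rho = 0.7. Without adjustment, power is about 60% at a standardised difference of 0.84 and 76% at 1.01; 80% needs about 1.06.

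**The case against.** The strongest reply is that the sentence has two halves. Persistence is looked for together with significant improvement by month 6. A reader might infer from the 97.5% that a lasting benefit would nearly always be declared for a treatment that does nothing. The article does not support that: the figure belongs to the month 6 to 7 check alone, and the joint vCR-arm pattern has about a 2% chance when nothing changes.

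Second, sham is not left out. It and month 7 are both in the 2 by 4 ANOVA, the sham expectation is stated, and the Summary and Outlook section gives efficacy compared with sham as the goal. This stands, but only so far. The arm-by-time term is an omnibus test over four visits. It can be significant because of months 3 or 6 alone, and it neither isolates nor estimates the month-7 difference.

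Third, the verbs are *hope* and *expect*, under a heading that includes anticipated results, so this is not a formal success rule. That is also right. Follow-up contrasts may be named in an analysis plan that is not shown, and their absence from an article would not be a finding. The point rests on the one reading of the pause that the article does give.

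A reader might also infer that persistence would usually be read even after most of the effect had gone. The figures do not bear this out. With three-quarters of a 0.84 SD effect lost, the check is passed 38%, 17% and 5% of the time at rho 0.5, 0.7 and 0.8.

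**Conclusion.** The point holds in limited form. A non-significant month 6 to 7 change in 15 vCR patients, without a margin, cannot reliably separate a kept benefit from one that has lost about half its size: the check is passed about 55% of the time at the pilot effect, and between 11% and 67% under the other effect sizes and correlations tried. The companion conditions deal with the case where nothing changes. They are still separate within-arm tests and do not compare the arms: with a moderate shared improvement, the whole pattern can arise up to about 24% of the time with no vCR effect, against 2.5% for a direct contrast.

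The within-arm results rest on the assumed SD and test sidedness, and the 24% is specific to a shared improvement of dz about 0.54. Severity is low to moderate: the primary time point is month 6, persistence is a supporting aim in a proof-of-concept study, and the text states an expectation.

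**What to change.** State the estimate of lasting effect as the baseline-adjusted vCR-minus-sham difference in off-medication MDS-UPDRS III at month 7, with its 95% CI. Report beside it the between-arm difference in the month 6 to 7 change, with its CI, to show whether the arms converge once stimulation stops. Present the month 6 to 7 change within the vCR arm as descriptive, or test it against a margin fixed in advance, and do not read its non-significance as persistence. If the analysis plan already names such a contrast, it should replace the arm-by-arm reading.

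This takes a change of wording and two contrasts on data already being collected, with no new visits or patients. The price is that persistence becomes harder to claim: with 30 patients the month-7 interval extends about 0.54 SD (adjusted, assumed correlation 0.7) to 0.75 SD (unadjusted) either side of the estimate.
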